#### 6.2.4.5 Statistical methods

The time between persistent cervical HPV infections and lesions will be analyzed using Kaplan-Meier method and Cox regression models.

Kaplan-Meier curves presenting the cumulative probability of lesions following 6-month persistent cervical HPV infections will be displayed and compared between groups for determinants of interest using the Log-rank test (univariate analyses). Cox regression models will be also performed for the univariate analyses in order to obtain unadjusted hazards ratios of the determinants of interest.

In addition, a multivariable Cox regression model will be performed in order to estimate the relative contribution of each determinant adjusting for the simultaneous effects of the other covariates. The model will include: time-independent covariates (e.g., age and region at study entry), time-independent covariates re-assessed at follow-up visits (e.g., behavioral determinants updated over the follow-up period using the yearly behavioral questionnaires) and time-dependent covariates (e.g., concomitant cervical HPV infections, i.e. co-infection). Also, some of the determinants will be distinguished depending on whether they started

before or after the 6-month persistent cervical HPV infections leading to the lesions in order to differentiate their effects in the pathway leading from cervical HPV infection to lesion (cf. Sections 4.4.2 and 4.4.3 for the definition of behavioral and clinical determinants and Section 8.5.1 for the list of determinants that will be taken into account in the analysis).

As the same subject may contribute to more than one observation (e.g., the same women may have several persistent cervical HPV infections of same or different HPV types leading or not to lesions associated with these HPV types), the analysis will be performed using an appropriate approach (counting process, clustering etc.) carried out either by a standard or a stratified Cox model depending on whether i) the recurrent events may be considered as identical or different and ii) the assumption that the estimated proportional hazards are constant over time is fulfilled or not [Andersen et al., 1993; Prentice et al, 1981; Kelly and Lim, 2000; Kleinbaum and Klein, 2005].

As the different events from a same subject are treated as independent observations in the Cox model, robust variance estimates adjusted for the correlation within subjects will be obtained using the robust estimation method derived as an extension of the information sandwich estimator [Lin and Wei, 1989; Zeger and Liang, 1986].

The choice of the best fitted model will be based on the Akaike's Information Criterion (AIC) and the Schwarz Bayesian Criterion (SBC) but also on the consistency of the effects of the covariates observed in the different multivariable models.

Results from the multivariable time survival analyses (Cox model) will include mean and median (if estimable) time (with 95% CI) and hazards ratios (with 95% CI). The survival curves predicted by the model will be displayed.

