#### 4.4.4 Other determinants

The following analysis factors will be defined at subject level using data from the CRF:

- Age groups (years) at the start date of time to event for each endpoint (cf. Section 8.5 for more details). This determinant will be analyzed primarily as a continuous variable. For exploratory purposes, it could also be categorized as followed: 15-17; 18-25.
- Geographical regions: Europe (Belgium, Finland, Germany, Italy, Spain, UK); Asia Pacific (Australia, Philippines, Taiwan, Thailand); Latin America (Brazil, Mexico); North America (Canada, United States).

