#### **4.5.2 Other missing data**

Missing and inconsistent data will not be replaced. Thus, subjects from the TVC-1- Control arm cohorts with a missing endpoint measure will not be included in the analyses related to this endpoint. Likewise, subjects with a missing or inconsistent data for a determinant (from behavioral questionnaire or CRF) will not be included in the analyses using this determinant.

In case too many observations have to be excluded due to missing data, data imputation may be performed on a case by case basis for some of the determinants used in the univariate and multivariable analyses.

The choice of the most appropriate imputation method (mean substitution, use of multiple regression etc.) will be done at the time of statistical analysis. It will depend on the percentages and patterns of missing data (missing at random or not). The chosen method will be described and justified in the statistical report.

All analyses performed based on imputed missing data will be considered as sensitivity analyses aimed at confirming or complementing the main results obtained without replacement of missing data.

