#### **6.1.2 Univariate and multivariable analyses**

Except for the analysis of time to first detected incident cervical HPV infection (or first confirmed persistent 6-month cervical HPV infection), the statistical unit of univariate and multivariable analyses will be the cervical HPV infection related to the analyzed event. In order for the determinants defined at subject level to be used in the analyses, the values of

these determinants will be attributed, for each subject, to all the cervical HPV infections of the subject.

The inclusion of determinants in the models will depend on the meaning of these determinants with regards to the analyzed endpoint. For instance, when analyzing the time to first cervical HPV infection, all determinants linked to cervical HPV infections occurring after the first cervical HPV infection will not be taken into account as determinants in the analysis (cf. Section 8.5 for the lists of determinants used in the analyses).

Changes in the definitions of determinants (i.e. modifications of categorizations) may be performed at the time of the statistical analysis in case:

- one category contains too few subjects as compared to the other modalities of a same factor,
- two highly correlated factors are statistically significant in the multivariable analyses. In such case, the two factors may be combined in one single categorisation or one factor will not be used in the analyses.
- a different expression of a determinant is more meaningful for the interpretation of the results, more particularly for determinants that show an association with the outcome (e.g. the effect of cigarette smoking could be assessed using the cumulative lifetime exposure to smoking rather than using the number of packs per year),
- specific analyses are performed (e.g. analyses restricted to HPV types 16 and/or 18).

Such changes will be documented and justified in the statistical report.

Although described in the frequency distribution tables, the modality “never had sexual intercourse” for some of the behavioral determinants may not be taken into account in the univariate and multivariable analyses.

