### 6.2.5.5 Statistical methods

The time between any cervical HPV infections and lesions will be analyzed using the same models and methodology as for the analysis of the time between persistent cervical HPV infections and lesions (cf. Section 6.2.4.5).

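### The Cox model is chosen by AIC/SBC (SAP 6.2.4.5), but nothing requires the candidate models to be fitted to the same infections, and 4.5.2 drops records determinant by determinant

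*SAP*

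**What the plan says.** - **Selection rule (SAP 6.2.4.5).** "The choice of the best fitted model will be based on the Akaike's Information Criterion (AIC) and the Schwarz Bayesian Criterion (SBC", and the sentence continues: "but also on the consistency of the effects of the covariates observed in the different multivariable models". No threshold or order of precedence is given for the second part.
- **Missing data (SAP 4.5.2).** "subjects with a missing or inconsistent data for a determinant (from behavioral questionnaire or CRF) will not be included in the analyses using this determinant". Imputation does not change the main model choice: "All analyses performed based on imputed missing data will be considered as sensitivity analyses".
- **Candidate models (SAP 6.1.2).** Determinants may be recategorised at analysis. Where two correlated factors are both significant, "the two factors may be combined in one single categorisation or one factor will not be used in the analyses". The category for women who never had intercourse may also be left out of the models.
- **Standard or stratified (SAP 6.2.4.5).** The analysis is "carried out either by a standard or a stratified Cox model depending on whether" recurrent events are alike or different and whether hazards are proportional. AIC/SBC is not named for this choice.
- **Reach.** Section 6.2.5.5 says the time from any infection to lesion "will be analyzed using the same models and methodology as for the analysis of the time between persistent cervical HPV infections and lesions", and 6.2.7.5 adopts the same methods for time to first infection.

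**The concern.** AIC and SBC rank models only when their likelihoods come from the same observations. In a Cox model they must also come from the same risk sets. Under 4.5.2 the records depend on which determinants are in the model, and no sentence requires a common set for the comparison. A determinant with missing values can then gain on AIC/SBC simply because its model contains fewer events.

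The study's schedule makes differing record sets likely. Questionnaires start at Month 1 (3.2), and behavioral determinants come from the last questionnaire before the reference infection was detected (4.4.3). Infections already present at Month 0 that persist are in the primary analysis (6.2.4.1). Read literally, these have no preceding questionnaire, so models with and without behavioral determinants would use different infections.

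The selected model supplies the adjusted hazard ratios for the primary objective. A wrong choice could keep an irrelevant determinant, or drop a relevant one, on a reduced and selected set of infections.

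**Working it through.** The SAP states no event count, missing-data rate or effect size for these analyses, so there is no figure of its own to reproduce. All sizes below are assumptions.

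**1. Size of the artefact.** −2 log partial likelihood is roughly 2·Σ ln(risk-set size) over events. With d events, typical risk set R and a share m of records missing at random:
- lost events lower it by about 2·d·m·ln R;
- thinner risk sets for the remaining events lower it by about a further 2·d·m;
- a real binary determinant with prevalence p lowers it by only about d·p(1−p)·(ln HR)².

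**2. Break-even missingness** (p = 0.5, R = 500 to 2,000). From lost events alone, m = 0.25·(ln HR)² / (2·ln R):
- HR 2: 0.1201/12.43 = 0.97% to 0.1201/15.20 = 0.79%.
- HR 3: 0.3017/12.43 = 2.4% to 0.3017/15.20 = 2.0%.

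Adding the second term (denominators 14.43 and 17.20) gives 0.7–0.8% for HR 2 and 1.8–2.1% for HR 3.

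**3. Simulation, real against noise determinant.** The real determinant is complete; the noise determinant is missing completely at random. There were 150 runs per setting, with 1,000, 3,000 or 5,000 infections and about 105–235 events. Share of runs in which AIC preferred the noise model:

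| Missing | Real HR 2 | Real HR 3 |
|---|---|---|
| 0.5% | 33–41% | 4–11% |
| 1% | 62–71% | 17–23% |
| 2% | 84–97% | 55–73% |
| 5% | 100% | 94–100% |
| 10% | 100% | 100% |

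SBC gave the same shares. With both models on the same records, the noise model won in 0–2.7% of runs in every setting. At 5% missing its mean AIC advantage was 53 to 176 points.

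Check on the largest of these (HR 2, 3,000 infections, about 229 events): 2·229·0.05·(ln 3000 + 1) − 229·0.1201 = 206 − 27.5 ≈ 179, against 176 simulated.

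**4. Adding a noise determinant to a model with the real one** (1,500 infections, about 157 events, HR 2). AIC's penalty is 2 and SBC's is ln 157 ≈ 5.1. One lost event is worth about 2·ln 1500 ≈ 14.6. At 1% missing, thinner risk sets alone give 2·157·0.01 ≈ 3.1. Two separate simulations had AIC add the noise determinant in 98–100% of runs at 1–5% missing, against 13–22% on identical records (nominal 16%). In one of them the change in the real determinant's hazard ratio was recorded: it was under 10% in 97–100% of runs.

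**5. Strata, only if AIC/SBC is applied across the two forms.** S equal, irrelevant strata lower −2 log partial likelihood by about 2·d·ln S. The SAP names no stratification factor; S = 4 is illustrative, matching its four regions (4.4.4). With 112.9 and 227.5 events on average, 2·d·ln 4 = 313 and 631. Subtracting the contribution of a real HR 3 (0.3017·d = 34 and 69) leaves 279 and 562. Simulation gave 281 and 570, with the stratified noise model preferred in 100% of runs.

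**The case against.** A reader might infer that the plan picks whichever model has more missing data or more strata, regardless of the determinants' effects. The document does not support that, for four reasons.

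- **AIC/SBC is not the only criterion.** The same sentence adds consistency of effects, and 6.1.2 brings clinical and virological meaning into interpretation. This stands, but it offers little protection: the criterion has no threshold, and in step 4 the real effect barely moved when the noise determinant was added, so the wrong model would look consistent.
- **Stratification has its own grounds.** Section 6.2.4.5 ties it to event type and proportional hazards. The strata problem therefore arises only if AIC/SBC is also compared across the two forms, which the text neither states nor excludes.
- **Effects do matter at low missingness.** Below the break-even values the real determinant usually wins.
- **Different records are a consequence, not a stated procedure.** The plan describes a multivariable model with determinants listed in 9.5.1 and no stepwise search. If 4.5.2 were applied once to the full list, all candidates would share one complete-case set. That reading is possible but not written, and 6.1.2 allows factors to be dropped or merged. HPV type, the main covariate, cannot be lost this way, because it defines the infection.

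Imputed sensitivity analyses are a partial safeguard, but they are optional and do not govern the main choice.

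**Conclusion.** The concern holds as a missing validity condition. Sections 4.5.2 and 6.2.4.5, followed literally, allow AIC/SBC to be compared between models fitted to different infections, where the comparison has no meaning. A few percent of missing values can then outweigh a real hazard ratio of 2–3: 94–100% wrong preferences at 5% missing, against at most 2.7% on common records. Below about 1% missing (HR 2) or 2% (HR 3) the real determinant usually prevails.

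These figures rest on assumed numbers of infections and events, 50% prevalence and data missing completely at random; they illustrate size and do not predict this study. The stratification part is conditional on AIC/SBC being used across standard and stratified models. The point should be corrected, because the selected model carries the primary objective and two further sections inherit the rule.

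**What to change.** In SAP 6.2.4.5, add:
- AIC and SBC are compared only among models fitted to the same infections (those complete on all candidate determinants), with the same stratification, risk sets and time scale.
- Standard or stratified is settled beforehand on criteria i) and ii) of that section, not by AIC/SBC.
- The chosen model is then refitted on all infections with its determinants available, and the number of infections and events is reported for both fits.

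Sections 6.2.5.5 and 6.2.7.5 inherit the change. The plan should also say how infections present at Month 0 obtain questionnaire values, since this decides whether they belong to the common set.

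**Cost.** The edit is wording. Selection uses a smaller subset and is somewhat less precise; the loss is unknown without missing-data rates and grows if Month 0 infections fall out. Section 7 records that the primary-endpoint analysis was delivered in August 2011, so that model choice should be checked against the rule and rerun if its candidates used different records.

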# 1 CONTEXT OF THE RAP DEVELOPMENT

This statistical analysis plan (SAP) describes the epidemiological approach used to investigate the progression from an initial cervical HPV infection to cervical pre-cancer and cancer. As most HPV infections are cleared by the immune system and do not result in clinical complications such as cervical pre-cancer and cancer, the clearance of HPV infections will be also investigated. In addition, the time to first HPV infection and to first persistent HPV infection will be explored.

Thus, the study objectives are to describe the following outcomes:

- i) the time between confirmed persistent cervical HPV infections and the development of CIN associated with the same HPV type,
- ii) the time between any cervical HPV infections and the development of CIN associated with the same HPV type,
- iii) the clearance of cervical HPV infections,
- iv) the time between the start of sexual activity and a first incident or a first persistent cervical HPV infection,

and to assess the effect on these outcomes of determinants such as sexual behavior, smoking history etc. known to predispose subjects to cervical HPV infections and/or clinical complications of HPV infections such as pre-cancer and cervical cancer.

The analyses will be performed using data obtained from the subjects included in the control arm of the HPV-008 study (End-of-Study (M48) database from the Phase III pivotal study to evaluate the efficacy of HPV-16/18 VLP AS04 vaccine compared with control HAV vaccine).

More specifically, analyses will include the use of the following data collected at enrolment and during all the visits over the 48-month follow-up of the control arm subjects included in the HPV-008 study:

- i) virological (cervical HPV infection detected by PCR in cervical liquid-based cytology (LBC) samples),
- ii) cyto-pathological examinations on LBC samples and histology samples (colposcopy performed according to the clinical management algorithms defined for the HPV-008 study),
- iii) HPV-16/18 serostatus (by ELISA) at enrolment,
- iv) socio-demographic and behavioral data.

Of note, the results of the analysis of the time between the start of sexual activity and a first incident or a first persistent cervical HPV infection will be presented in a stand-alone statistical report.

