**Figure 1 Study Overview**

[figure not shown]

- **Experimental design:** A phase III, controlled, multi-center (n=135), and multi-country (n=14) study with two parallel groups.
- **Treatment Groups:** 2 groups: vaccine and control
  - Vaccine: 20µg HPV-16 L1 VLP/20µg and HPV-18 L1 VLP/50µg MPL®/ 500µg aluminum in the form of Al(OH)3,
  - Control: Hepatitis A vaccine (Havrix™-based investigational formulation) (720 ELISA units of antigen; 500µg aluminum in the form of Al(OH)3).
- **Treatment allocation:** Randomized (1:1).

- **Randomization method:** SBIR (Internet randomization).
- **Blinding:** Double-blind.
- **Enrolment period:** May 2004 to June 2005.
- **Study regions:** Asia Pacific, Europe, Latin America and North America.
- **Enrolled:** 18729 subjects aged 15-25 years. Total Vaccinated Cohort (TVC): 18644 subjects. Total Vaccinated Cohort for efficacy 1 (TVC-1): 18525 subjects.
- **Control arm** (HAV vaccine group): TVC: 9325 subjects. TVC-1: 9267 subjects.
- **Vaccination schedule(s):** Three doses of HPV vaccine or HAV vaccine (control arm) administered on a Month 0, 1, 6 schedule.
- **Study visits:** 10 study visits per subject scheduled at Months 0, 1, 6, 7, 12, 18, 24, 30, 36 and 48.
- **Total duration of the study:** 48 months of follow-up from study entry planned for all subjects.
- **Database freeze for the final analysis:** October 2008; **Database freeze for the M48 analysis:** March 2010.

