#### **6.2.4.4 Time computation**

The time between the onset of a confirmed persistent cervical HPV infection (6-month definition) and a histopathologically-confirmed CIN2+ (or CIN1+, or CIN3+) associated with the same HPV type will be calculated in days as: Date of event or Date of censoring - Date of detection of the 6-month HPV persistent infection.

The date of event will be:

- the date of the detection of the histopathologically-confirmed CIN2+ (or CIN1+, or CIN3+) associated with the same HPV type as the HPV type of the 6-month persistent cervical HPV infection,

The date of censoring will be:

- the date of Month 48 visit for subjects who attended all visits during the 48-month follow-up period and who had a histopathologically-confirmed CIN2+ (or CIN1+, or CIN3+) not associated with the same HPV type as the 6-month persistent cervical HPV infection or who did not have a histopathologically-confirmed CIN2+ (or CIN1+, or CIN3+) or during this period,
- the date of the last PCR reported at the latest visit for which data are available or the date of the last cytology or the date of the last biopsy (if the date is after the date of the last PCR) for subjects who did not attend all visits during the 48-month follow-up period and who had a histopathologically-confirmed CIN2+ (or CIN1+, or CIN3+) not associated with the same HPV type as the 6-month persistent cervical HPV infection or who did not have a histopathologically-confirmed CIN2+ (or CIN1+, or CIN3+) throughout their follow-up period (from first to last visit).
- Special cases:
  - In case two distinct 6-month persistent cervical HPV infections (i.e. separated by a clearance) associated with the same HPV type are detected for a same subject and a histopathologically-confirmed CIN2+ (or CIN1+, or CIN3+) associated with this HPV type is detected after the second infection, the date of censoring of the first infection will be the date of onset of the second infection since the event (i.e. detection of a histopathologically-confirmed CIN2+ (or CIN1+, or CIN3+)) is associated with the second detected infection (in chronological order).

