| #2 |         | HPV16   |          |          |              |          |              |          | n        | NA    |               | 
 
Subject #2 had a transient HPV16 cervical infection detected at month 6 but no 6-month persistent cervical HPV infection throughout the 48-month follow-up period.
 
No persistent cervical HPV infection is included in the analysis (subject not included in the analysis).
 
                                                                                                                          |
| #3 |         |         | HPV 16   | HVP16    |              |          |              |          | y        | n     | 36 (censored) | 
 
Subject #3 had a 6-month persistent HPV16 cervical infection detected at month 12 and no CIN detected throughout the 48-month follow-up period.
 
One persistent cervical HPV infection is included in the analysis with a censored time-to-event value of 36 months and HPV type = 16.
 
                                                                                                                |
| #4 |         |         |          | HPV18    | HPV18        |          | CIN3 (HPV33) |          | y        | n     | 24 (censored) | 
 
Subject #4 had a persistent HPV18 cervical infection detected at month 24 and a CIN3 associated with HPV33 at month 42.
 
One persistent cervical HPV infection is included in the analysis with a censored time-to-event value of 24 months and HPV type = 18 (note: time-to-event value is censored because CIN3 is not associated with the same HPV type as the persistent cervical HPV infection).
 
 |

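### SAP 6.2.4.5 promises a mean time to lesion with a 95% CI but sets no restriction time, although every infection is censored at Month 48 or earlier

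*SAP*

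**What the plan says.** The primary objective (SAP 2.1) is to describe the time from onset of a 6-month persistent infection to CIN2+ of the same HPV type, and the effect of determinants on it. Section 6.2.4.5 plans Kaplan-Meier curves with log-rank tests, univariate Cox models and a multivariable Cox model that may be standard or stratified. The sentence on what will be reported reads: "Results from the multivariable time survival analyses (Cox model) will include mean and median (if estimable) time (with 95% CI) and hazards ratios (with 95%".

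Follow-up is bounded. Section 3.1 gives "48 months of follow-up from study entry planned for all subjects". Section 6.2.4.4 censors lesion-free infections at "the date of Month 48 visit for subjects who attended all visits during the 48-month follow-up period", and at the last available PCR, cytology or biopsy for the others. The plan's own example in 9.4.1, with onset at Month 12 and no lesion, enters the analysis "with a censored time-to-event value of 36 months and HPV type = 16".

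Section 1 says that "most HPV infections are cleared by the immune system and do not result in clinical complications such as cervical pre-cancer and cancer". No progression rate is given anywhere.

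Section 6.2.5.5 carries the methods over: time from any infection to lesion "will be analyzed using the same models and methodology as for the analysis of the time between persistent cervical HPV infections and lesions". Section 6.2.7.5 does the same for time from start of sexual activity to first infection. No section states a restriction time, an estimator for the mean, or a horizon common to the categories compared.

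**The concern.** A mean survival time is the whole area under the survival curve. If the curve is still above zero when follow-up ends, the remaining area is unobserved, and what can be computed is the area up to some cut-off. With no cut-off stated, the reported number depends on a choice made at analysis. Its confidence interval reflects sampling error only and not the missing tail.

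Time to CIN is what the primary objective sets out to describe, so a mean with a 95% CI would be read as how long progression takes. If the cut-off also differs between HPV types or regions, the means are not comparable with one another.

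The estimability qualifier follows the word median, and the sentence does not settle whether it also covers the mean.

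**Working it through.** **Inputs from the SAP.** Follow-up of 48 months from entry (3.1). Censoring at the Month 48 visit or earlier (6.2.4.4). PCR sampling at Months 0, 6, 12, 18, 24, 30, 36 and 48 (3.2). Seven HPV-type categories (4.4.2).

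**Assumed.** Lesion risk by 48 months (P) from 1% to 50%, exponential times. The SAP gives no rate, event count or mean, so there is no figure to reproduce. The arithmetic of its worked examples does check: 48 − 12 = 36 and 48 − 24 = 24 (censored), 30 − 6 = 24 (event), 48 − 6 = 42 (9.4.2), and 48 + 6 = 54 (9.4.3).

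**Step 1: time available.** Follow-up from onset is 48 minus the onset month: 48 months for onset at Month 0, 36 at Month 12, 24 at Month 24, and 12 at Month 36.

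**Step 2: full mean against what can be observed.** λ = −ln(1 − P)/48; mean = 1/λ; median = ln 2/λ; area to 48 months = (1 − e^(−48λ))/λ = P/λ. For P = 50%, λ = 0.693/48 = 0.01444, so the mean is 69 and the area is 0.5/0.01444 = 34.6.

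| P by 48 months | Full mean (months) | Median (months) | Area to 48 months |
|---|---|---|---|
| 1% | 4776 | 3310 | 47.8 |
| 5% | 936 | 649 | 46.8 |
| 10% | 456 | 316 | 45.6 |
| 20% | 215 | 149 | 43.0 |
| 30% | 135 | 93 | 40.4 |
| 50% | 69 | 48 | 34.6 |

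The full mean assumes that every infection would eventually progress. If some never do, it is infinite.

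**Step 3: standard Cox model, shared baseline, one horizon of 48 months.** Reference risk 15%, so λ = 0.1625/48 = 0.003386 and the area is (1 − e^(−48λ·HR))/(λ·HR). Hazard ratios of 0.1, 0.3, 1 and 2 give 47.6, 46.9, 44.3 and 41.0 months. The order follows the hazard ratio, but a 20-fold range of hazard (2/0.1) appears as a ratio of 47.6/41.0 = 1.16.

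**Step 4: separate curves, each cut at its own last event.** 2000 simulated data sets per scenario: onset spread over Months 0 to 36 (30% at Month 0), lesions found at 6-month steps, censoring at Month 48. Runs with no event in a group were dropped, leaving 1932 runs in row 2, 1887 in row 3, and all 2000 elsewhere.

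| Lower risk (n) | Higher risk (n) | Average means, lower / higher | Lower-risk group shows the shorter mean |
|---|---|---|---|
| 1% (1500) | 15% (500) | 42.5 / 44.4 | 53% |
| 1% (500) | 15% (400) | 33.3 / 44.1 | 80% |
| 2% (200) | 15% (200) | 31.6 / 42.4 | 77% |
| 2% (1500) | 15% (500) | 45.2 / 44.4 | 31% |
| 5% (1500) | 15% (500) | 46.6 / 44.4 | 6% |
| 5% (300) | 25% (300) | 41.7 / 42.0 | 51% |
| 10% (300) | 30% (300) | 43.4 / 41.0 | 29% |

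No scenario reached a median. With the same data cut at a common 36 months, the order was never reversed (first row: 35.9 against 34.2 months).

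**The case against.** **The sentence concerns the Cox model.** A reader might infer that the plan will rank low-risk HPV types as progressing fastest, against its own hazard ratios. The SAP does not support that. Step 3 shows that a standard Cox model with one baseline and one horizon cannot reverse the order. Reversal needs category-specific cut-offs, from group-wise Kaplan-Meier areas or a Cox model stratified on the determinant compared. Section 6.2.4.5 allows stratification, but in connection with recurrent events and the proportional-hazards assumption, and names no stratifying variable. The SAP also does not say how its software would cut a mean: section 6.1.1 names SAS and no procedure. The reversal is therefore conditional, and its frequency (6% to 80% above) depends on assumed risks and group sizes.

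**The qualifier may cover the mean.** This is a fair reading, and on it a mean that cannot be estimated would not be printed. The sentence then leaves the primary objective without any prespecified numerical time summary wherever neither quantity is estimable, so the wording still needs changing.

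**Section 1 speaks of HPV infections in general.** It would be tempting to say that a median within 48 months contradicts the plan. Section 1 gives no rate for 6-month persistent infections, nor for CIN1+ as against CIN3+, so that inference fails for the primary analysis. The case against the mean does not need it, as the 50% row of Step 2 shows.

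**Section 6.2.7.5 has a different event.** Low progression to lesions says nothing about how soon first infection occurs. Only the missing horizon carries over.

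**Curves, hazard ratios and event densities are already planned** (6.2.3.1, 6.2.4.5). They limit the damage, but they do not make the mean interpretable.

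**Conclusion.** The point holds as a defect in the stated summary measure. With censoring at Month 48 or earlier and no restriction time, an unrestricted mean time to lesion is not estimable unless the curve reaches zero. A printed mean would understate time to progression and mostly describe follow-up. Under exponential times the shortfall runs from about a factor of 2 at an assumed 50% risk (69 against 34.6 months) to about a factor of 100 at 1% (4776 against 47.8). These sizes rest wholly on assumed rates. The direction does not: an area cut short cannot exceed the whole.

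Misordering of categories is possible only under an estimator that the plan leaves open. Hazard ratios, log-rank tests and the planned curves are unaffected. The change is worth making because the affected figure is the numerical answer to the descriptive half of the primary objective.

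**What to change.** In 6.2.4.5, and so in 6.2.5.5 by reference, replace the mean and median wording with text to this effect:

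- Report the cumulative probability of CIN2+ (or CIN1+, CIN3+) at fixed times after infection onset, for example 12, 24 and 36 months, overall and by determinant, with 95% CIs robust to within-subject correlation.
- Give the median only where the curve crosses 50%.
- Report any mean only as a restricted mean to one prespecified horizon common to all categories, labelled as such.

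The times are proposals and do not come from the SAP. Only infections with onset by Month 12 can be followed for 36 months (48 − 12 = 36), so numbers at risk should be shown at each time.

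For 6.2.7.5, add equivalent wording for first infection, or first 6-month persistent infection, since the start of sexual activity, with its own common horizon. The CIN wording cannot simply be inherited there.

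The cost is a few lines of SAP text and a small table from curves already planned. The downside is that no single unrestricted average time is reported.
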